### Limitations

Individuals with pre-diabetes and diabetes are randomized in the same group and it can be discussed whether the same decline in HbA_1c_ can be expected in individuals with pre-diabetes. Furthermore the participants in the control group may be influenced by participating in a research study and being assessed regularly. As they agree to join they are highly motivated to change their physical activity level and we expect many of them to succeed in this by their own. This could make comparison of between-group differences problematic. Moreover, the control group is assessed by the same staff as group A and B, for practical and financial reasons. This staff is trained in motivational interviewing and it might be difficult to treat the patients differently. At measurements participants from group A, B and C are given different schedules, group A participants are offered more time and a systematic motivational interviewing following a set of questions.

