#### Inclusion criteria

Age 40-80 years and ability to communicate in Swedish. Either Pre-diabetes (HbA_1c_ > 39- < 47 mmol/mol and/or fasting glucose >5.6 mmol/l) or diagnosed with type 2 diabetes with a duration of ≥1 year.

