### Procedure and timeline

The baseline measurements start with an examination by the patient’s general practitioner for exclusion purposes. A notification is made on subjects not fulfilling the criteria at this stage. The study-specific measurements are made by the diabetes specialist nurse or a trained assistant, followed by randomization to three groups using closed envelopes while stratified by gender. The participants are randomly assigned to either the multi-component intervention group (A), the single component group (B) or a control group (C). A total of 310 patients with pre- diabetes or type 2 diabetes will be included gradually, with the aim of 100 participants included in group A and B, and 110 in the control group C by the end of 2017. After randomization, participants are given a schedule for measurement time points and group A participants receive a schedule for group sessions and individual consultations. The intervention lasts for 24 months, with more intensive support from the health care professionals within the first 24 weeks, and less support in the second year (Fig. 2).

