### Sample size and planned statistical analysis

The sample size calculation assumed 80 % power and was calculated drawing on previous literature [14, 66] by statistical power analysis. To detect a difference of > 0.6 mmol/mol in HbA_1c_ with a standard deviation of 1.2 % at 12 months between group A and B and between group A and C we need 56 per group. Taking account the compliance and drop-out (30 %) and patients which decline participation (20 %) we need in group A 100 patients, in group B 100 patients and in group C 110 patients.

The study will be evaluated with both quantitative and qualitative methods and a cost-effectiveness analysis will be performed. The CONSORT 2010 statement will be used for description and analysis [45]. Data will be analyzed following the Intent-to-treat approach (ITT). Descriptive statistics will be used to describe the study population at baseline. The study data will be examined for outliers, normality and missing data. Potential confounders as (e.g. BMI at baseline, gender and age) will be used if there are differences at baseline.

Un-paired and paired tests, correlation coefficients as well as ANOVAs will be used to assess the bivariate effects of the interventions and to analyze within-group and between-group differences and changes. In addition, logistic regression models and/or cluster analyses will be performed to analyze issues related to dose–response and responder characteristics. SPSS 22 (SPSS Inc., Chicago, IL, USA) will be used for the statistical analysis.

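### Diabetes status, defined partly by the primary outcome, is not a randomisation stratum or a fixed covariate; adjusting for it in every case would be more precise than the stated rule

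*Protocol article*

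**What the plan says.** - **Population** (Inclusion criteria). Pre-diabetes is "HbA_1c_ > 39- < 47 mmol/mol and/or fasting glucose" above 5.6 mmol/l; the alternative is "or diagnosed with type 2 diabetes with a duration of ≥1 year".
- **Numbers** (Procedure and timeline). "A total of 310 patients with pre- diabetes or type 2 diabetes will be included gradually". No share or cap by diabetes status is given.
- **Randomisation** (same section). Baseline measurements are "followed by randomization to three groups using closed envelopes while stratified by gender". No other stratum is named.
- **Sample size** (Sample size and planned statistical analysis). One effect and one SD serve the whole sample: "To detect a difference of > 0.6 mmol/mol in HbA_1c_ with a standard deviation of 1.2 % at 12 months".
- **Analysis** (same section). Between-group comparisons use unpaired tests and ANOVA. Covariates are given as examples, "Potential confounders as (e.g. BMI at baseline, gender and age", and are used only where the arms differ at baseline. Logistic regression or cluster analysis is planned for dose-response and for the characteristics of responders. Diabetes status is named in neither place.
- **Limitations**. The two populations share the same groups, and "it can be discussed whether the same decline in HbA_1c_ can be expected in individuals with pre-diabetes". The article draws no consequence from this for randomisation, sample size or analysis.

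**The concern.** Diabetes status is known before randomisation and is tied to the primary outcome by definition, so it should be among the strongest predictors of 12-month HbA1c. If it is left out of the comparison, the HbA1c gap between the two populations becomes part of the residual variance. A rule that adjusts only after a baseline difference is seen makes the primary model depend on the data, and in most realisations it gives up the precision that this factor offers.

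The trial's own authors also doubt that the effect is the same in both populations. A single pooled difference is then an average weighted by a mix that is not planned. Without estimates by status, a modest pooled result would be hard to read: it could mean a modest effect in everyone, or a useful effect in type 2 diabetes averaged with little in pre-diabetes.

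**Working it through.** **Inputs from the protocol.** Difference 0.6, SD 1.2, power 80 %, 56 per group before inflation, 100 in groups A and B and 110 in C, drop-out 30 %. Analysed numbers after drop-out: 100 × 0.7 = 70 and 110 × 0.7 = 77.

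**Assumed, because the protocol does not give them.** Two-sided alpha 0.05. Both 0.6 and 1.2 are read in percentage points (the printed units conflict, which is a separate matter). Pre-diabetes share p of 20-50 %. SD 0.3 in pre-diabetes and 1.2 in type 2. Mean 12-month HbA1c gap between the populations 1.0 point, taken as the same in both arms. Effect 0.6 in type 2 and r × 0.6 in pre-diabetes, with r = 0 or 0.5.

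**The plan's own figure.** n per group = 2 × (1.96 + 0.84)² × (1.2/0.6)² ≈ 63, not 56; power at 56 is about 75 %. That shortfall is a separate fault and is not counted here. At 70 and 77 analysed, with 0.6 in everyone and SD 1.2, power is 85 %.

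**Formulas.**
- Pooled effect: d = 0.6 × [1 − p(1 − r)].
- Within-status variance: W = (1 − p) × 1.44 + p × 0.09.
- Between-status variance: B = p(1 − p) × 1.0².
- SD without adjustment is √(W + B); SD with status in the model is √W.
- SE = SD × √(1/70 + 1/77) = SD × 0.165.
- Power is that of a two-sided two-sample t-test; the normal approximation is up to about 1 percentage point higher.

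**Standard deviations.**
- p = 0.2: W = 1.170, B = 0.160. SD 1.15 unadjusted, 1.08 adjusted.
- p = 0.5: W = 0.765, B = 0.250. SD 1.01 unadjusted, 0.87 adjusted.

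| p | r | d | d/SE unadjusted | Power unadjusted | d/SE adjusted | Power adjusted |
|---|---|---|---|---|---|---|
| 0.2 | 0 | 0.48 | 2.52 | 71 % | 2.69 | 76 % |
| 0.5 | 0 | 0.30 | 1.80 | 43 % | 2.08 | 54 % |
| 0.2 | 0.5 | 0.54 | 2.84 | 80 % | 3.02 | 85 % |
| 0.5 | 0.5 | 0.45 | 2.71 | 77 % | 3.12 | 87 % |

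Adjustment adds 5 to 11 percentage points. Two things would shrink the gain. Analysing change from baseline already removes much of the gap between the populations. A smaller gap also reduces B; if type 2 patients alone respond, the gap narrows in the active arm, so the 1.0 is best read as an average over the arms.

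**Worst case, for reference only.** With no effect in pre-diabetes and the SD held at 1.2 for everyone, power is 56-26 % at 56 per group and 67-32 % at 70 and 77.

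**Chance imbalance.** The SD of the difference in pre-diabetes share between arms is √[p(1 − p)(1/70 + 1/77)], about 7 percentage points at p = 0.2 and 8 at p = 0.5. Times a 1.0-point gap, this is 0.07-0.08, against a standard error of about 0.17-0.19 (1.01 × 0.165 and 1.15 × 0.165) that already contains it.

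**Interaction test.** For a full 0.6 difference in effect with common SD 1.2, SE = 1.2 × √[2/(np) + 2/(n(1 − p))]. Power is 18-26 % at n = 56 and 29-42 % at n = 100 per group, for p from 0.2 to 0.5.

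**The case against.** **Condensed article.** Model detail is commonly left to the SAP, and an unseen plan may name status. The covariate list is introduced as examples, and the analysis of responder characteristics could include status. This stands as far as it goes: status is unnamed, not ruled out, and the absence of an interaction test is no finding. But the gender-only stratification and the covariate rule that depends on baseline differences are positive statements, and they are what the point rests on.

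**The 39-47 band.** A reader might infer that a fall of 0.6 percentage points, about 6.6 mmol/mol at an assumed 10.9 per point, cannot be expected in pre-diabetes because it is some 80 % of an 8 mmol/mol band. The protocol does not support that. Patients may enter on fasting glucose alone, so the band does not bound HbA1c in this group. Entry limits do not bound follow-up values. The 0.6 is a difference between groups, not a fall within patients. And as printed it is in mmol/mol.

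**Low power.** A reader might also take 26-56 % as the trial's real power. Those figures assume no effect at all in pre-diabetes, whereas the Limitations section questions only an equal decline, and the Background reports preventive effects in impaired glucose tolerance. They also hold the SD at 1.2 where it is probably much smaller, and take 0.6 as the type 2 effect, which the protocol does not say.

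**Imbalance.** Chance imbalance under randomisation is not bias, and the standard error covers it. This stands; the argument for adjustment is precision.

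**Timing.** Recruitment began in November 2013, so a new stratum helps only patients still to come. This also stands, and it makes adjustment the main remedy.

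**Conclusion.** The point holds as one of precision and interpretability. Pooling the two populations is a disclosed choice and not an error. The weakness is that a factor tied to the primary outcome, and doubted by the authors themselves as regards equal response, has no fixed place in randomisation or analysis. Under the assumptions stated, unconditional adjustment for status is worth about 5 to 11 percentage points of power for the 12-month comparison, and less if change from baseline is analysed. It does not undo any dilution of the pooled effect. How large that dilution is cannot be known from the protocol, since neither the pre-diabetes share nor the effect there is given. It is a cheap improvement and not a flaw that invalidates the trial.

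**What to change.** 1. Include diabetes status at baseline, together with baseline HbA1c, in the primary 12-month HbA1c model, whatever baseline differences are seen.
2. Report the between-group difference at 12 months separately for pre-diabetes and type 2 diabetes, as estimates with confidence intervals. Do not rest a conclusion on the interaction test, which is underpowered.
3. For patients still to be randomised (inclusion runs to the end of 2017), stratify the envelopes by gender and diabetes status if practical, and include the stratification factors in the analysis.

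Optional: allow the residual variance to differ by status, and state power under a mixed effect once an expected pre-diabetes share can be given.

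Cost: analysis wording and four envelope stacks instead of two. No new data are needed, because status is known at entry and HbA1c at baseline and 12 months is already in Table 1. The estimates by status will be imprecise and should be presented as such.

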## Discussion

With an ageing population and increasing incidence of pre-diabetes and diabetes, it is of high importance to construct, implement and evaluate cost-effective preventive methods adjusted for the health care system [41]. It is well-documented that walking, exercise groups and advice on prescription are effective at a low cost per participant over 12 months [34]. It is known that more support gives more long-term effect, although it is also evident that rather simple interventions can provide a worthwhile effect [67]. This study aims at bringing more knowledge to what intensity such methods need to be at, to be as cost-effective as possible. Long-term interventions are rare in diabetes intervention research [41]. This study will show if support for two year’s maintenance is effective. A further strength is that it brings theory into practice and adds evidence for methods by which behavior change techniques may be delivered and embedded in the day to day care in a time-effective way [43, 68]. The methods used and evaluated in Sophia Step Study may be easily implemented in the primary health care setting with little new competence and administrative time needed. The study aims to raise the patient’s awareness and self-management and assess the impact of self-perceived general health, as proposed by the US National Standards for Diabetes Self-Management Education and Support [69], WHO Europe’s policy framework Health 2020 [26] and value-based care [70] which is being implemented in Sweden.

### Ethical considerations

Ethical approval was obtained from the ethics committee of the Regional Ethical Review Board (Dnr.2012/1570-31/3). All participants receive both oral and written information and are asked to give written informed consent prior to participating. The participants are informed that the data is treated confidently. All data will be stored anonymous with only the ID-code and analysis will be made only at group level. The study will be carried out in accordance with the ethical principles of the World Medical Association Declaration of Helsinki: ethical principles for medical research involving human subjects (2013).
